**Methods/Design:**

This is a randomized controlled trial with 2-arms parallel. Fifty-five moderate or severe asthmatics with grade II obesity (BMI ≥ 35 kg/m^2^) under optimized medication will be randomly assigned into either weight-loss program + sham (WL + S group) or weight-loss program + exercise (WL + E group). The weight loss program will be the same for both groups including nutrition and psychological therapies (every 15 days, total of 6 sessions, 60 min each). Exercise program will include aerobic and resistance muscle training while sham treatment will include a breathing and stretching program (both programs twice a week, 3 months, 60 min each session). The primary outcome variable will be asthma clinical control. Secondary outcomes include HRQL, levels of depression and anxiety, lung function, daily life physical activity, body composition, maximal aerobic capacity, strength muscle and sleep disorders. Potential mechanism (changes in lung mechanical and airway/systemic inflammation) will also be examined to explain the benefits in both groups.

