As previously discussed, asthma and obesity are clinical conditions characterized by chronic inflammation; the effects of exercise have been evaluated in the setting of each condition but not in the setting of both diseases together. Our hypothesis is that exercise training amplifies weight loss and exerts both anti-inflammatory and immunoregulatory effects, resulting in improved clinical control and quality of life, as well as improved psychosocial symptoms and sleep disorders among obese asthmatic patients. The objective is to assess the effects of exercise training in a weight-loss program on asthma control, quality of life and psychosocial symptoms in obese patients with stable asthma.

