#### Statistical analysis

An intention-to-threat analysis will be used to preserve the effects of group allocation and provide an assessment of the practical impact of the treatment [74], as recommended by the CONSORT statement [75]. The normality of continuous outcomes will be assessed via the Kolmogorov-Smirnov test. Comparisons of the initial and final data will be analyzed via a two-way repeated-measures analysis of variance, and the categorical outcomes, via the *χ*^2^ test. A partial correlation will be used to test the effects of airway and systemic inflammation as mediators. P values ≤ 0.05 will be considered statistically significant. The statistical analysis will be blinded to the treatment allocation and will be performed using specific software (SigmaStat 3.5, Systat Software Inc.).

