The possible mechanisms underlying the improvements in patients’ physical fitness may be related to changes in lung mechanics and either systemic or airway inflammation. We expect that the addition of exercise training may have clinical benefits (reduced symptoms) among obese asthmatic patients by decreasing asthma allergic inflammation [28], as well as by amplifying weight loss by increasing metabolic consumption, which may subsequently decrease the low grade inflammation commonly noted among patients who are obese [33, 34]. Weight loss exerts positive effects on lung function among subjects with and without asthma [80] via improvements in chest wall compliance secondary to reduced mass loading effects caused by fat accumulation in and around the chest wall. If our hypothesis is correct, reductions in body weight will improve ventilation efficiency by improving chest wall compliance.

Improvements in physical fitness may reduce the levels of pro-inflammatory mediators observed in subjects with low-grade inflammation (high-sensitivity C-reactive protein, IL-6, TNF-α, MCP-1, IL-8, and leptin) [81–83] and increase the levels of anti-inflammatory markers and mediators (adiponectin and IL-10) [32–34]. We expect that exercise training will facilitate decreases in the levels of the systemic biomarkers that contribute to the pathogenesis of asthma, as it has been demonstrated previously that aerobic conditioning improves airway inflammation via reductions in FeNO levels among patients with asthma [28]. It has also been suggested that exercise training modulates allergic inflammation by increasing the expression of the anti-inflammatory cytokines IL-10 and IL-1ra in an animal model of asthma [84]. We hypothesized that there is a correlation between reduced FeNO, a marker of airway inflammation, and increased levels of these anti-inflammatory cytokines. Another possible effect of improved physical fitness is an improved quality of sleep and a reduction in psychological symptoms, as the prevalence of anxiety and depression are significant in both patients with asthma [85] and patients who are obese [85–87].

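### Partial correlation is named as the test of inflammation as a mediator, but it does not test mediation, and a marker that exercise did not change can pass it

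*Protocol article*

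**What the plan says.** The protocol article, Statistical analysis, gives one sentence on mediation: "A partial correlation will be used to test the effects of airway and systemic inflammation as mediators". It does not say which variables are correlated, whether changes or final values are used, or what is held constant. The decision rule is the general one: "P values ≤ 0.05 will be considered statistically significant". The same section plans a comparison over time: "Comparisons of the initial and final data will be analyzed via a two-way repeated-measures analysis of variance". Nothing links that comparison to the mediator claim.

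The mechanisms of interest are described more widely elsewhere. The Background states: "Our hypothesis is that exercise training amplifies weight loss and exerts both anti-inflammatory and immunoregulatory effects, resulting in improved clinical control". The abstract states: "Potential mechanism (changes in lung mechanical and airway/systemic inflammation) will also be examined to explain the benefits in both groups". The Discussion says that mechanisms "may be related to changes in lung mechanics and either systemic or airway inflammation".

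**The concern.** A mediator of the exercise effect has to satisfy two conditions. Allocation must change it (path a), and it must affect the outcome given allocation (path b). The mediated effect is the product of the two. The sentence in the plan names a tool that looks at one link only, and attaches to it a claim that needs both.

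The setting makes this more than a formal point. Both arms receive the same nutritional and behavioural programme. If weight loss from that shared programme moves both inflammation and ACQ, the two will correlate within each arm even if exercise does nothing to inflammation. Randomisation protects the arm comparison of the marker; it does not protect the marker-ACQ link.

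At stake is the published explanation of how exercise works, which the abstract and Discussion present as a purpose of the trial. The primary result is not at stake.

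**Working it through.** The plan gives no figure for the mediation analysis, so there is none to reproduce. The check asks what the named test responds to.

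**Inputs from the protocol article.** 55 patients and up to 20 % loss (Sample size): 55 × 0.80 = 44 completers. Threshold 0.05 (Statistical analysis).

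**Assumptions (the documents give no values).** Within-arm marker-ACQ correlation r from 0 to 0.5; exercise effect on the marker a = 0; direct effect of exercise on ACQ 0.7 SD, close to the plan's own 0.5/0.72 = 0.69.

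**Model.** With arm A, marker M and outcome Y: M = a·A + error; Y = c·A + b·M + error. The mediated effect is a·b. If a = 0 it is zero whatever b is. Marker and outcome have within-arm SD 1, so b equals r when a = 0.

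**Reading 1: marker with ACQ, given arm.** Degrees of freedom are 44 − 3 = 41, so t = 2.02 and the critical |r| is 2.02/√(41 + 2.02²) = 0.301. By Fisher's z the standard error is 1/√(44 − 1 − 3) = 0.158. The chance of significance is Φ(atanh(r)/0.158 − 1.96) plus the small opposite tail. Simulated columns use 5,000 trials per setting.

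| r | atanh(r)/0.158 | Significant, 44 patients (Fisher z) | Simulated, 44 | Simulated, 55 |
|---|---|---|---|---|
| 0 | 0 | 5 % | 4.4 % | 5.1 % |
| 0.1 | 0.63 | 10 % | not run | not run |
| 0.2 | 1.28 | 25 % | not run | not run |
| 0.3 | 1.96 | 50 % | 49.7 % | 61.1 % |
| 0.4 | 2.68 | 76 % | not run | not run |
| 0.5 | 3.47 | 94 % | 94.0 % | 97.5 % |

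True mediation is zero in every row.

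**Does the test notice path a?** At b = 0.5 and 44 patients it is significant in 94.0 % of trials when a = 0 and in 94.3 % when a = 0.7. With 55 patients both figures are 97.5 %. It does not distinguish a marker that exercise changed from one that it did not.

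**Requiring both paths.** With a = 0 the arm-marker test rejects in about 5 % of trials, so both reject in about 0.05 × 0.50 = 2.5 % at r = 0.3 and 0.05 × 0.94 = 4.7 % at r = 0.5. Simulated: 2.3 % and 4.1 % with 44 patients; 2.9 % and 4.7 % with 55.

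**Reading 2: arm with ACQ, given the marker.** With a = 0 and a direct effect of 0.7 SD, this is significant in 59 %, 66 % and 74 % of trials for b = 0, 0.3 and 0.5 with 44 patients, and in 72 %, 75 % and 84 % with 55. With no direct effect (a = 0, b = 0.5) it falls to about 5 %. It follows the direct effect, so it does not test mediation either.

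**The case against.** **Both paths are in the plan.** FeNO and blood markers are measured before and after in both randomised arms, so the group-by-time term of the ANOVA speaks to path a and a partial correlation given arm speaks to path b. This stands in part. A reader might infer that the trial would have no randomised evidence on whether exercise changed a marker; the documents do not support that. What remains is that the mediator sentence names the correlation alone as the test, and that the ANOVA result is not a condition for the claim.

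**The test is underspecified, and an article may leave details to the analysis plan.** True, and the missing detail is not the complaint. The article fixes the method and the claim, and neither natural way of filling in the detail tests mediation.

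**The percentages restate the assumption.** Correct. They are the power to detect a correlation that was put in. A reader might take 50 % to 94 % as the rate at which this trial would mislead. The documents give no marker-ACQ correlation, and at 0 to 0.2 the rate is only 5 % to 25 %.

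**Weight and lung mechanics.** A reader might infer that the trial ignores these hypothesised routes. It does not: both are measured and open to the ANOVA, pulmonary function stands under Evaluating possible mechanisms, and further mediation models are detail that a condensed article may leave out.

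**Consequence is limited.** Mechanisms are called possible or potential, and the objective in the Background covers asthma control, quality of life and psychosocial symptoms. This limits the weight of the point but does not remove it.

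**Conclusion.** The concern holds in a limited form. The plan names a method that cannot establish the claim attached to it. Given arm, the partial correlation assesses only the marker-outcome link; given the marker, only the direct effect. As written, a marker unaffected by exercise can be declared a mediator.

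How often that would happen depends on a correlation that the documents do not give. With 44 completers it ranges from about 5 % with no correlation to 94 % at 0.5, against at most about 5 % if both paths are required. The figures illustrate the logic under a simple linear model without baseline adjustment; they are not a forecast. The logical point needs none of them. It bears on the mechanism conclusions only.

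**What to change.** Replace the mediation sentence with wording such as:

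> For each pre-listed airway or systemic marker we will estimate (a) the effect of arm on the final marker, adjusted for its baseline, and (b) the effect of the final marker on final ACQ, adjusted for arm, baseline ACQ and baseline marker. The indirect effect a·b will be reported with a bootstrap 95 % confidence interval. These analyses are exploratory. Partial correlations will be reported as associations only.

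The exploratory label is needed because mediator-outcome confounding remains under this model too. Order in time does not help: within each evaluation, ACQ is taken on day 2 and FeNO and blood markers on day 3 (Experimental design).

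As a secondary suggestion, weight change and lung volumes can go through the same model, since the Background, abstract and Discussion name them as routes.

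The cost is a wording change and modest analysis on data already planned. Whether the named software can bootstrap should be checked. Intervals will be wide: even with sizeable assumed paths (a = 0.7, b = 0.5), both path tests are significant together in only about 58 % of trials with 44 patients and 70 % with 55.

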#### Airway inflammation

Airway inflammation will be quantified using the exhaled fraction of nitric oxide (FeNO), using a portable analyser (NIOX MINO®; Aerocrine AB, Solna, Sweden), in accordance with ATS/ERS guidelines [72]. The patients will be asked to exhale fully while seated before inhaling through a NIOX filter until they will reach their total lung capacity, and immediately will exhale at a constant flow rate of 50 ml/s using a visual feedback system. The average levels of at least 3 acceptable measurements will be used. The patients will be instructed to avoid eating foods containing nitrate and caffeine and to avoid smoking and exercise 24 h before testing, as well as to refrain from ingesting either food or water for at least 2 h before testing. NO collection will be performed by the same professional at the same time of day in order to avoid changes in patients’ circadian rhythms. A cut off point of 25 parts per billion (ppb) will be used to either confirm or exclude a diagnosis of eosinophilic airway inflammation [72].

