#### Systemic inflammation

Patients’ inflammatory systemic profiles will be assessed using blood-based markers. Venous blood samples will be collected following at least 8 h of overnight fasting, and the patients will be advised to avoid exercise, alcoholic and caffeinated beverages 24 h before testing. The cytometric bead array method (BD Biosciences, San Jose, CA, USA) will be used to analyse the levels of IL-1, IL-2, IL-4, IL-5, IL-6, IL-8, IL-10, IL-12, IL-13, TNF-α, vascular endothelial growth factor (VEGF), T-cell receptor beta (TGF-β) and the chemokines MIG/CXCL9, IP-10/CXCL10, IL-8/CXCL8, MCP-1/CCL2 and RANTES/CCL5. Serum leptin, adiponectin, CRP (ELISA, MILLIPORE), cortisol (Siemens, Immulite 200) and vitamin D (Ria-CT) levels will also be analyzed.

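### One unadjusted P ≤ 0.05 threshold covers 22 mechanism markers, so isolated significant markers are weak evidence for the anti-inflammatory part of the hypothesis

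*Protocol article*

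**What the plan says.** The Statistical analysis section gives the method for continuous outcomes, "Comparisons of the initial and final data will be analyzed via a two-way repeated-measures analysis of variance", and one threshold without qualification: "P values ≤ 0.05 will be considered statistically significant". The same section also plans partial correlations that test airway and systemic inflammation as mediators, and these fall under the same threshold.

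The markers are listed under Evaluating possible mechanisms. Airway inflammation is measured by FeNO. The Systemic inflammation section names a bead-array panel of cytokines and growth factors, then "and the chemokines MIG/CXCL9, IP-10/CXCL10, IL-8/CXCL8, MCP-1/CCL2 and RANTES/CCL5", and adds: "Serum leptin, adiponectin, CRP (ELISA, MILLIPORE), cortisol (Siemens, Immulite 200) and vitamin D (Ria-CT) levels will also be analyzed".

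The Background states the hypothesis that "exercise training amplifies weight loss and exerts both anti-inflammatory and immunoregulatory effects", leading to better asthma control and quality of life. No marker or summary is named as the one that decides this part of the hypothesis. The Discussion does predict directions for some markers, beginning: "Improvements in physical fitness may reduce the levels of pro-inflammatory mediators observed in subjects with low-grade inflammation". It expects CRP, IL-6, TNF-α, MCP-1, IL-8, leptin and FeNO to fall, and adiponectin and IL-10 to rise. The analysis section makes no use of these predictions.

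**The concern.** The inflammatory effect is not incidental. It is written into the hypothesis, and the Abstract says that mechanisms will be examined to explain the benefits in both groups. The plan gives a reader one tool for judging it: a P value of 0.05 or less, marker by marker, over a long list. IL-2 or vitamin D then counts the same as IL-6 or CRP.

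At stake is a mechanism claim built after the fact on whichever markers cross the threshold. With a panel of this length, one or more crossings are likely by chance alone, and the mediator analyses could then be centred on those same markers. Once the results are known, the choice of which markers matter cannot be made credible.

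**Working it through.** **Inputs from the article**
- Threshold per test: 0.05 (Statistical analysis).
- Cytokines and growth factors: IL-1, IL-2, IL-4, IL-5, IL-6, IL-8, IL-10, IL-12, IL-13, TNF-α, VEGF, TGF-β = 12.
- Chemokines: five entries, but IL-8/CXCL8 repeats IL-8, so 4 more.
- Other serum markers: leptin, adiponectin, CRP, cortisol, vitamin D = 5.
- Airway marker: FeNO = 1.
- Distinct markers: 12 + 4 + 5 + 1 = 22, of which 21 are blood markers.
- Markers with a predicted direction (Discussion): 7 down + 2 up = 9. The other 13 have none stated there.
- Evaluable patients: 55 × 0.80 = 44, taken as 22 per arm (Sample size; equal allocation assumed).

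**Inputs assumed**
- One group-by-time test per marker, equivalent to a two-sample t-test on change.
- A common correlation between markers from 0 to 0.7. The article gives none.

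The article states no error rate for the marker panel, so there is no figure of its own to reproduce.

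**Independent markers, no effect**
- At least one P ≤ 0.05 in either direction: 1 − 0.95^22 = 0.676.
- At least one in a favourable direction (0.025 per test): 1 − 0.975^22 = 0.427.

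**Correlated markers, no effect** (400,000 draws of equicorrelated normal statistics, 22 tests)

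| Correlation | Any marker, either direction | Any marker, favourable direction |
|---|---|---|
| 0 | 67.6 % | 42.8 % |
| 0.1 | 66.0 % | 38.1 % |
| 0.3 | 56.8 % | 29.6 % |
| 0.5 | 43.9 % | 22.1 % |
| 0.7 | 30.1 % | 15.0 % |

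Simulated trials with 22 patients per arm and t-tests agree within simulation error: 67 %, 58 %, 43 % and 32 % at correlations 0, 0.3, 0.5 and 0.7, and about 43 % down to 16 % for favourable changes only. The favourable column assumes that every marker has a favourable direction. The Discussion supplies one for only nine.

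**How far an any-marker reading separates effect from no effect.** With a true shift of 0.5 SD in all nine predicted markers and correlation 0.3, the chance of at least one P ≤ 0.05 rises from 58 % to 96 %. With 21 independent markers it rises from 65.9 % under no effect to only 77.8 % when a single marker truly shifts by 0.5 SD.

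**Benjamini-Hochberg over all 22.** With no effect, it flags any marker in about 3–5 % of trials over this range of correlations. Its strictest step is 0.05/22 = 0.0023. With a 0.5 SD shift in all nine predicted markers, it flags at least one marker in 49 % (correlation 0.1) or 40 % (0.3) of trials.

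**A global score over the nine predicted markers** (mean standardised change, with adiponectin and IL-10 sign-reversed). It rejects about 5 % of the time under no effect. Its power is 95 % (correlation 0.1) or 74 % (0.3) if all nine shift by 0.5 SD, but only about 9–22 % if just two or three do.

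**The case against.** The strongest reply is that the article contains no any-marker rule. A reader might infer that the anti-inflammatory conclusion rests on 22 separate tests, with a significant change in either direction counting as success. The article does not say so. It gives a conventional significance level, and the Discussion sets out directions against which two-sided results would naturally be read. This stands: the percentages describe what happens if isolated crossings are taken as evidence, which the article permits but does not prescribe.

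A reader might also infer that the rule cannot discriminate at all, or that chance supplies a significant marker in most trials without an effect. Neither is supported. Discrimination is poor when one marker responds and good when many do, and at a correlation of 0.5 or more the chance of a false crossing is below one half. Restricting attention to favourable changes in the nine predicted markers lowers it further: 1 − 0.975^9 = 20 % if they are independent.

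These are mechanism analyses. The single primary outcome is the ACQ, and the stated objective names asthma control, quality of life and psychosocial symptoms, not inflammation. That stands and limits the importance of the point.

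Finally, multiplicity for mechanism markers is often left to a full protocol or SAP, and neither is shown. The mere lack of an adjustment would therefore be no finding. But the article does fix a threshold, without qualification, for a set of tests that serves a stated hypothesis. Applying that threshold as written gives an unreliable mechanism claim.

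**Conclusion.** The point holds in a limited form. One unadjusted threshold is applied to 22 distinct markers that bear on a stated hypothesis, and nothing links the hypothesis to particular markers. With no exercise effect, the chance of at least one nominally significant marker is about 67 % under independence, falling to 32 % at correlation 0.7. For favourable changes only it is about 43 % to 16 %, which is still roughly three to nearly nine times the nominal 5 %. These figures rest on assumed equal correlations, one test per marker and 22 evaluable patients per arm. The rates under no effect depend little on the number of patients; the power figures do depend on it.

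Isolated significant markers would be weak evidence for the mechanism. The primary comparison of ACQ change is not affected.

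**What to change.** In the Statistical analysis section, before unblinding:
1. State that the 22 between-group marker comparisons will be reported with Benjamini-Hochberg-adjusted P values.
2. State that the anti-inflammatory hypothesis will be read against the nine markers whose direction the Discussion already predicts, and list them with those directions.
3. Label the other 13 markers exploratory.
4. Leave the ACQ analysis as it is.

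The global score over the nine markers may be added as a supplementary analysis. It should not be the sole basis for the conclusion, because it loses most of its power when only two or three markers respond and because it merges airway with systemic inflammation.

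The cost is a few sentences and a few lines of code. All markers are already to be measured, and no patients are added. The price is lower power for individual markers, and a lone marker with unadjusted P ≤ 0.05 would no longer count as evidence of an anti-inflammatory effect. When some markers truly change, the adjustment controls the expected share of false findings, not the chance of any false finding.

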## Discussion

The association between asthma and obesity is an interesting issue since the pathogenesis of asthma is altered in obese asthmatics because they do not respond as well to standard controller asthma therapy. The inclusion of evidence-based weight loss strategies is recommended by the GINA guidelines in spite of the lack of trials demonstrating the intervention that is most effective in facilitating weight loss in obese asthmatics [18, 22].

The aim of the present study is to assess the effects of exercise training in the setting of a weight loss intervention on asthma control, quality of life and psychosocial symptoms in obese asthmatics. It is important to understand the role of exercise as part of a comprehensive weight loss program in these patients, as well as to investigate possible mechanisms by which improvements in physical fitness result in improvements in both clinical and psychological variables. Additionally, sedentary lifestyle and deconditioning both play key roles in the development of respiratory symptoms in obese asthmatic patients [76]. Furthermore, exercise is associated with improvements in airway hyperreactivity [23], psychosocial factors [24], health related quality of life [25] and reduced airway inflammation [28] among patients with asthma. Additionally, exercise exerts positive effects on body weight, cardiovascular disease risk factors and systemic inflammation among patients who are obese [32–34, 77].

Nevertheless, we are aware of only 2 studies investigating the effects of physical fitness among obese asthmatic [22, 78]. Scott et al. [22] conducted a randomized trial involving 46 overweight and obese adults with asthma who were allocated to 3 distinct groups as follows: a calorie-restricted diet group, an exercise training group and a group receiving both interventions. Contrary to our study hypothesis, the authors observed that exercise training did not provide benefits in terms of weight loss and improvements in clinical control on a calorie-restricted diet program. It is important to note that they did not observe improvements in physical activity levels following their exercise training program and did not perform evaluations pertaining to improvements in physical fitness [22]. A possible explanation for their findings is that their patients participated in a greater amount of physical activity at baseline (61 % reported participating in vigorous activity, and 24 % reported participating in moderate physical activity). Furthermore, they were already close to the 10.000 steps/day threshold, suggesting they were physically active with respect to international guidelines [79]. A recent trial [78] investigated the effects of an evidence-based comprehensive weight loss intervention composed of diet, physical activity and behavioural therapy compared with standard therapy in obese asthmatics. In spite of the inclusion of a comprehensive weight loss intervention, the physical activity program in this study included recommendation to maintain a minimum of 150 min of physical activity per week and not a supervised exercise protocol. The patients in the intervention group experienced significantly more weight loss compared with the control subjects (respectively, −4.0 ± 0.8 kg vs. -2.1 ± 0.8 kg); however, neither group observed any changes in either ACQ or the numbers of asthma exacerbations.

The possible mechanisms underlying the improvements in patients’ physical fitness may be related to changes in lung mechanics and either systemic or airway inflammation. We expect that the addition of exercise training may have clinical benefits (reduced symptoms) among obese asthmatic patients by decreasing asthma allergic inflammation [28], as well as by amplifying weight loss by increasing metabolic consumption, which may subsequently decrease the low grade inflammation commonly noted among patients who are obese [33, 34]. Weight loss exerts positive effects on lung function among subjects with and without asthma [80] via improvements in chest wall compliance secondary to reduced mass loading effects caused by fat accumulation in and around the chest wall. If our hypothesis is correct, reductions in body weight will improve ventilation efficiency by improving chest wall compliance.

Improvements in physical fitness may reduce the levels of pro-inflammatory mediators observed in subjects with low-grade inflammation (high-sensitivity C-reactive protein, IL-6, TNF-α, MCP-1, IL-8, and leptin) [81–83] and increase the levels of anti-inflammatory markers and mediators (adiponectin and IL-10) [32–34]. We expect that exercise training will facilitate decreases in the levels of the systemic biomarkers that contribute to the pathogenesis of asthma, as it has been demonstrated previously that aerobic conditioning improves airway inflammation via reductions in FeNO levels among patients with asthma [28]. It has also been suggested that exercise training modulates allergic inflammation by increasing the expression of the anti-inflammatory cytokines IL-10 and IL-1ra in an animal model of asthma [84]. We hypothesized that there is a correlation between reduced FeNO, a marker of airway inflammation, and increased levels of these anti-inflammatory cytokines. Another possible effect of improved physical fitness is an improved quality of sleep and a reduction in psychological symptoms, as the prevalence of anxiety and depression are significant in both patients with asthma [85] and patients who are obese [85–87].

In conclusion, this study will bring a significant contribution to the literature evaluating the effects of exercise conditioning in a weight loss program; the results may facilitate improvements in asthma control, quality of life and psychosocial symptoms and help elucidate the possible mechanisms underlying the improvements in lung function, as well as both airway and systemic inflammation, among obese asthmatic patients.

